### Statistical Plan

Statistical analysis on LUT, bowel and sexual function will be performed (n = 40 with SCI).

A sample size calculation was performed using G\*power, version 3.0.10, with power set at 0.8 and  $\alpha$  at 0.05. Data from participants that match our inclusion criteria (n = 5, level of lesion C5 – T10, motor-complete AIS, A or B) were used from a recent TCSCS study. A minimum sample of 26 participants is required to detect a significant change in voiding efficiency [voided volume / (voided volume + post-void residual volume)] with short-term TCSCS (stim-off =  $37.8 \pm 40.6\%$  vs. stim-on =  $58.2 \pm 39.4\%$ , effect size = 0.510). Presently, there are no long-term TCSCS data with LUT and bowel outcomes, consistent with those proposed in this protocol, to facilitate a meaningful power calculation. Therefore, given this is a pilot trial study, and in order to account for drop out with long-term TCSCS, we aim to investigate 40 individuals with SCI (n = 40, C5 – T6). Short-term TCSCS effects on UDS parameters (AIM 2A) as well as ARM testing (AIM 2C) with or without different stimulation configurations will be assessed using a repeated measures non-parametric analysis of variance (ANOVA), i.e. Kruskal–Wallis test. Data from the repeatability portion of the study (AIM 2A) will be assessed within (same session) and between (different sessions) visits (2 and 3) using a repeated measures non-parametric ANOVA. TNFBM will also be assessed using a repeated measures non-parametric ANOVA.

Long-term TCSCS: Differences in continuous variables for questionnaire data (NBSS, NBD Score, I-QoL, IIEF-15 or FSFI) in AIM 3 will be assessed using a two-way repeated measures [baseline, immediately post long term TCSCS as well as post-interventional follow up at 6 and 12 weeks] ANOVA comparing changes between moderate and intensive TCSCS. Furthermore, UDS testing as well as 'faecal continence severity' (baseline and end of TCSCS 6-week period) will be assessed using Wilcoxon signed-rank tests within

groups. A P-value less than 0.05 will be considered statistically significant. A complete thematic analysis will be performed to collect contextual qualitative data from the sexual health interview.

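### The Statistical Plan calls for a repeated-measures non-parametric analysis of Aims 2A and 2C but names Kruskal–Wallis, a test for independent groups; run as named, it would be conservative and lose power whenever off and on values are positively correlated

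*Protocol*

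**What the plan says.** The Protocol's Statistical Plan states that short-term effects on urodynamic parameters (Aim 2A) and manometry (Aim 2C), across stimulation configurations, "will be assessed using a repeated measures non-parametric analysis of variance (ANOVA), i.e. Kruskal–Wallis test". Repeatability is given a repeated-measures non-parametric ANOVA with no test named. For time needed for bowel movement, "TNFBM will also be assessed using a repeated measures non-parametric ANOVA", again with no test named.

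The design is within-person. Under Urodynamics, a standard assessment is followed by one with stimulation in the same participant. Under ARM, the measurement is repeated with stimulation. Outcome 2A is defined as change from baseline.

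On sample size, the same section has "power set at 0.8" and alpha 0.05, an "effect size = 0.510", and the statement "A minimum sample of 26 participants is required to detect a significant change in voiding efficiency". Enrolment is set higher: "we aim to investigate 40 individuals with SCI". The significance rule is "A P-value less than 0.05 will be considered statistically significant". For the long-term before/after urodynamic comparison, the section names the Wilcoxon signed-rank test, which is a paired test.

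**The concern.** Kruskal–Wallis ranks all observations together and compares rank sums between groups that it takes to be independent. It has no term for the participant. Applied to off and on values from the same people, it leaves stable between-person differences in the error. The plan's own SDs suggest that these differences are large (40.6 and 39.4 around means of 37.8 and 58.2). With positive within-person correlation, the reference distribution is then too wide: the test rejects too rarely under the null and misses real effects too often.

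The "i.e." reads as the plan's definition of its repeated-measures test. An analyst who follows the named test would run an unpaired analysis of the short-term efficacy aims. An analyst who follows the description would run something else. Choosing between them after the data are in would look post hoc.

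**Working it through.** **Inputs (Protocol, Statistical Plan).** Voiding efficiency off 37.8 (SD 40.6) and on 58.2 (SD 39.4); effect size 0.510; alpha 0.05; power 0.80; minimum 26; planned enrolment 40. Not stated: sidedness and the off/on correlation r. I take r from 0 to 0.8.

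**1. Reproduce the effect size.** Difference = 58.2 − 37.8 = 20.4. Pooled SD = √[(40.6² + 39.4²)/2] = √1600.36 = 40.00. Then 20.4/40.00 = 0.510, as stated.

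This is a difference over the between-person SD. The paired effect is dz = 20.4/√(40.6² + 39.4² − 2r × 40.6 × 39.4). At r = 0.5 it is 20.4/√1601.08 = 0.510; at r = 0 it is 0.361; at r = 0.75 it is 0.721. Using 0.510 as a paired effect therefore implies r of about 0.5.

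**2. Reproduce the 26.** Exact noncentral-t power with effect 0.51 and alpha 0.05:

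| Analysis | One-sided | Two-sided |
|---|---|---|
| Paired t, n needed for 0.80 | 26 (power 0.812) | 33 (power 0.811) |
| Paired t, power at n = 26 | 0.81 | 0.71 |
| Unpaired t, n per condition | 49 | 62 |

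Of these, only the one-sided paired calculation returns 26. The sample size therefore appears to rest on a paired analysis, although the text does not say so.

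**3. Why the unpaired test is conservative.** For two conditions of equal SD, the variance of the mean difference is 2σ²(1 − r)/n, but an unpaired test uses 2σ²/n. A nominal cut-off of 1.96 then acts like 1.96/√(1 − r). At r = 0.3 this is 2.34 (two-sided error about 0.02). At r = 0.5 it is 2.77 (about 0.006). At r = 0.8 it is 4.38 (below 0.001). The rank test behaves in nearly the same way.

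**4. Simulation of the named test.** Paired normal data with the stated means and SDs, n = 40, 40,000 runs per cell, rejection at two-sided 0.05:

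| Assumed r | Kruskal–Wallis power | Signed-rank power | Kruskal–Wallis actual type I error |
|---|---|---|---|
| 0 | 0.60 | 0.59 | 0.05 |
| 0.3 | 0.61 | 0.74 | 0.02 |
| 0.5 | 0.62 | 0.87 | 0.01 |
| 0.8 | 0.70 | 1.00 | 0.00 |

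Runs of a few thousand replicates scatter by about 0.02 around these values (for example 0.62 to 0.64 for Kruskal–Wallis at r = 0.5, and 0.68 to 0.71 at r = 0.8).

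**5. Would renaming the test to Friedman be enough?** With two conditions, Friedman reduces to a sign test. At n = 40 and r = 0.5 its power is about 0.67, against 0.87 for the signed-rank test. For the off/on contrast it would restore the design match but recover little power.

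**The case against.** The strongest reply is that this is a naming slip. The sentence describes the design class correctly, and the same section uses a signed-rank test for other paired data. Friedman may well have been meant, and then no power is lost to an unpaired analysis. This stands as a limit: the loss arises only if the name prevails over the description. It does not remove the contradiction, which nothing else in the protocol resolves.

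Four stronger readings are tempting, and the document does not support them.

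- A reader might infer that the loss is established. It depends on r, which the protocol does not give, and at r = 0 there is none.
- A reader might set Kruskal–Wallis at n = 26 (power about 0.39 at r = 0.5) against the planned 0.80 and blame the test for the whole gap. A two-sided signed-rank test at 26 reaches only about 0.69, so part of the gap comes from sidedness. Planned enrolment is also 40, not 26.
- A reader might take the figures as the power of Aims 2A and 2C. They are for voiding efficiency, which is neither among the six parameters of Outcome 2A nor the resting pressure of Outcome 2C. No power can be computed for those.
- A reader might extend the error to repeatability and time needed for bowel movement. Those sentences carry only the label, which suits their design. They need clarifying and are not themselves wrong.

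It is also fair to say that, under positive correlation, the error does not inflate false positives, and that the study describes itself as a proof of concept and pilot.

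**Conclusion.** The point holds as a self-contradiction in the protocol: the named test does not fit the within-person design of Aims 2A and 2C, nor the paired analysis on which the minimum of 26 appears to rest. The consequence is conditional. If Kruskal–Wallis is run as named and off and on values are positively correlated, type I error falls below 5% and power drops. At 40 participants the loss against a two-sided signed-rank test is nil at r = 0, about 13 points at 0.3, about 24 to 25 at 0.5 and about 30 at 0.8.

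These sizes assume normal data, a shift of 0.51 SD taken from voiding efficiency, and no dropout. Voiding efficiency is bounded at 0 to 100% with SDs near 40, so exact values would differ. The mismatch between test and design depends on none of these assumptions.

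**What to change.** In the Statistical Plan, replace Kruskal–Wallis as follows:

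- **Off versus on:** Wilcoxon signed-rank test.
- **Three or more conditions that every participant receives:** Friedman test.
- **Configurations that differ between participants, or incomplete blocks:** a mixed model with condition as fixed effect and a participant random effect. This case is likely to matter, because the Urodynamics section has the configuration optimised for each individual and Friedman needs the same complete set of conditions in everyone.

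Add a clause saying that the repeated-measures non-parametric ANOVA for repeatability and for time needed for bowel movement means these same within-person methods, not Kruskal–Wallis.

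The cost is one or two sentences in the protocol, carried into any statistical analysis plan, with no new data and no change to visits. The only further work is to state which stimulation conditions enter the multi-condition comparison. This should be settled before the short-term data are analysed.

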## Objectives, Hypotheses and Outcomes

**Objective 1:** To establish specific spatiotemporal activation maps for TCSCS at various spinal cord segments known to be involved in LUT and bowel control.

**Hypothesis 1:** In light of recent findings on the efficacy of spinal cord stimulation to improve bowel and LUT function, the optimal setting for motor responses (i.e. mapping) will be revealed during TCSCS.

**Primary outcome 1:** An individualized TCSCS map (i.e. location and stimulation parameters) to elicit optimal skeletal muscle activation corresponding to spinal cord segments involved in LUT and bowel control

**Objective 2:** To test whether targeted short-term TCSCS is safe with respect to cardiovascular consequences (e.g. autonomic dysreflexia) and can repeatedly improve LUT and bowel functions in humans with chronic SCI.

**Objective 2A) LUT function (safety/efficacy):** To test whether targeted short-term TCSCS is safe and can induce detrusor contractions (*voiding function*) while relaxing the EUS, i.e. to avoid DSD and independently enhance EUS tone (*storage function*).

**Hypothesis 2A):** In light of recent findings demonstrating TCSCS improves LUT function, we hypothesize that short-term TCSCS will improve voiding and storage functions without ACVEs.

**Outcome 2A):** Changes from baseline in the following UDS parameters for bladder capacity/compliance:

- i. Volume at the first sensation
- ii. Intravesical pressure (Pves) at the first sensation
- iii. Volume at the leakage point
- iv. Pressure at the leakage point
- v. Maximum bladder volume
- vi. Pves at the maximum bladder volume

**Objective 2B) LUT function (repeatability of TCSCS to improve UDS parameters):** To test whether targeted short-term TCSCS will repeatedly improve UDS parameters across different stimulation sessions.

**Hypothesis 2B):** TCSCS will elicit reproducible improvements in UDS parameters without ACVEs.

**Outcome 2B):** Reproducibility of changes within urodynamic parameters during stimulation will be assessed during two consecutive urodynamic procedures. UDS parameters for bladder capacity/compliance:

- i. Volume at the first sensation
- ii. Pves at the first sensation

**Objective 2C) Bowel function (safety/efficacy):** To test whether targeted short-term TCSCS is safe and can result in an immediate increase in anorectal pressure.

**Hypothesis 2C):** TCSCS will increase anorectal pressure without adverse cardiovascular effects.

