### Inclusion and Exclusion Criteria

#### *Inclusion:*

A participant with SCI must meet all of the following criteria in order to be eligible for inclusion:

1. Resident of British Columbia, Canada with active provincial medical services plan
2. Male or female, 18-65 years of age
3. Chronic traumatic SCI (non-progressive, with complete motor paralysis) at or above the T6 spinal segment.
4. >1-year post injury, at least 6 months from any spinal surgery.
5. Documented presence of bladder dysfunction
6. Documented presence of bowel or sexual dysfunction.
7. American Spinal Injury Association Impairment Scale (AIS) A, B.
8. Greater than or equal to antigravity strength in deltoids and biceps bilaterally
9. Hand function sufficient to perform Clean Intermittent Catheterization (CIC) or a committed caregiver to provide CIC for management of urinary bladder drainage.
10. Participants must have documented three days of bladder and bowel history prior to their baseline visit.
11. Willing and able to comply with all clinic visits and study-related procedures.
12. Able to understand and complete study-related questionnaires (must be able to understand and speak English or have access to an appropriate interpreter as judged by the investigator).
13. No painful musculoskeletal dysfunction, unhealed fracture, pressure sore, or active infection that may interfere with testing activities.
14. Medication dosage must be stable for period of 4 weeks prior to participation
15. Baclofen dose cannot exceed 60mg per day
16. Stable management of spinal cord related clinical issues (i.e., spasticity management).
17. Women of childbearing potential must not be intending to become pregnant, currently pregnant, or lactating. The following conditions apply:
  - a) Women of childbearing potential must have a confirmed negative pregnancy test prior to the baseline visit.
  - b) Women of childbearing potential must agree to use adequate contraception during the period of the trial. Effective contraception includes abstinence.

18. Must provide informed consent.

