#### Visit 2: Baseline Assessments – Weeks 3-4:

Approximately 1 hour.

All eligible participants will undergo baseline evaluation for severity of bladder, bowel, sexual and cardiovascular dysfunctions using the validated questionnaires listed below. Participants will also undergo baseline 24 hours ambulatory evaluation of cardiovascular functions. This test will be specifically scheduled on the day of bowel routine with detailed documentation of time of bowel routine and each of the bladder catheterisations.

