### *Visit 3 /Baseline EMG Mapping of Spinal Cord Segments with TCSCS / Week 3-4*

Approximately 2 hours.

Participants will undergo baseline mapping using surface EMG (Delsys Inc., Natick, USA) and concentric needle EMG as per an established protocol to record muscle activation during transcutaneous spinal cord stimulation (mapping) (TESCoN, SpineX Inc., CA, USA) at different spinal cord levels and different intensity. Please see subsections entitled TCSCS, Surface EMG and Concentric Needle EMG in Descriptions of Assessments section for details.

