### *Visits 4,5,6: Urodynamics and Anorectal Manometry – Weeks 4-6:*

Approximately 2.5 hours per visit.

Following Visits 1 (Screening) Visit 2 (baseline assessments) and Visit 3 (mapping visit) using a randomized counter-balanced approach, all individuals will be allocated into two distinct pathways:

- Pathway #1: individuals will start with Urodynamics, (UDS 1, Visit 4), followed by a second session of Urodynamics (UDS 2, Visit 5), and ARM (Visit 6).
- Pathway#2: individuals will start with ARM (Visit 4), followed by Urodynamics (UDS 1, Visit 5), and a second session of Urodynamics (UDS 2, Visit 6)).

TCSCS and Cardiovascular monitoring will be performed during UDS and ARM. Please see Description of Assessments for details of Urodynamics, ARM, TCSCS and Cardiovascular monitoring.

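### Repeatability is assigned to the wrong aim and to two visits without urodynamics, and the only between-session method named tests for a difference, so it cannot measure agreement

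*Protocol*

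**What the plan says.** Under Objectives, Hypotheses and Outcomes, repeatability is Objective 2B. It asks whether short-term stimulation improves urodynamic parameters again in a different session. Outcome 2B reads: "Reproducibility of changes within urodynamic parameters during stimulation will be assessed during two consecutive urodynamic procedures". It lists two parameters, volume and intravesical pressure at first sensation. Outcome 2A lists these two and four more, at the leakage point and at maximum bladder volume.

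The Statistical Plan introduces the analysis as "Data from the repeatability portion of the study (AIM 2A" and says these data "will be assessed within (same session) and between (different sessions) visits (2 and 3) using a repeated measures non-parametric ANOVA". It states no decision rule for repeatability and names no agreement measure.

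The visit headings are "Visit 2: Baseline Assessments – Weeks 3-4" and "Baseline EMG Mapping of Spinal Cord Segments with TCSCS / Week 3-4". For Pathway 1, the section on Visits 4, 5 and 6 says "individuals will start with Urodynamics, (UDS 1, Visit 4), followed by a second session of Urodynamics (UDS 2, Visit 5), and ARM (Visit 6". Pathway 2 begins with anorectal manometry at Visit 4 and has UDS 1 at Visit 5 and UDS 2 at Visit 6. Inclusion criterion 7 admits "American Spinal Injury Association Impairment Scale (AIS) A, B".

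**The concern.** The Statistical Plan and the visit schedule disagree on where the repeatability data come from, and the Statistical Plan and the objectives disagree on which aim the analysis serves. No single pair of visit numbers can repair this, because the right pair depends on the pathway.

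The method is the larger matter. Outcome 2B concerns whether the change under stimulation is reproducible. A repeated measures test on ranks asks whether one session tends to give higher values than the other. Two sessions can have the same average change while individual changes bear no relation to one another, and such a test would not notice. What is at stake is whether Aim 2B can answer its own question.

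**Working it through.** **Visits and aim, side by side (Protocol)**

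| Item | Statistical Plan | Objectives and visit sections |
|---|---|---|
| Aim for repeatability | 2A | 2B |
| Visit 2 | source of repeatability data | questionnaires, 24-hour blood pressure, diary |
| Visit 3 | source of repeatability data | EMG mapping |
| UDS 1 and UDS 2, Pathway 1 | not named | Visits 4 and 5 |
| UDS 1 and UDS 2, Pathway 2 | not named | Visits 5 and 6 |

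Neither pathway has urodynamics at Visit 2 or 3. Visit 5 is UDS 2 in Pathway 1 but UDS 1 in Pathway 2, so the analysis has to be indexed by session.

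**The protocol's own figure.** There is none for repeatability. The only computed sample size, 26, is for voiding efficiency. It is reproduced by a one-sided paired t-test at effect size 0.510, α 0.05 (power 0.812); two-sided, 33 would be needed. Nothing below depends on it.

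**What a test of differences says about agreement.** Let a person's change at session j be the sum of a person effect with variance ICC and independent error with variance 1 − ICC, with equal session means. A valid 5% test is then non-significant with probability 1 − 0.05 = 0.95 at any ICC. A simulation with normal data confirms it. It used 4,000 trials per cell for two sessions (Wilcoxon signed-rank) and 1,500 for four repeated readings (Friedman). The ICCs are assumptions. Percentage non-significant at n = 40:

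| ICC | Two sessions | Four readings |
|---|---|---|
| 0 | 95.0 | 94.9 |
| 0.2 | 95.1 | 94.9 |
| 0.5 | 95.6 | 95.3 |
| 0.9 | 95.3 | 93.8 |

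At n = 20 and n = 26 the values run from 94.6 to 96.3.

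Over the same range, agreement itself changes greatly. The SD of the between-session difference, in units of the SD of one session's change, is √(2(1 − ICC)). That gives √2 = 1.41 at ICC 0 and √0.2 = 0.45 at ICC 0.9. The 95% limits of agreement are ±1.96 times this: ±2.77 and ±0.88. The test result does not respond to that threefold difference.

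**If the sessions really differ.** Take an assumed true shift of 0.3 SD of the differences, a two-sided paired t-test at 0.05 and the noncentral t distribution. The probability of non-significance is 0.54 at n = 40, 0.69 at n = 26 and 0.75 at n = 20. Non-significance is weak evidence even that the means are equal.

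**What an agreement estimate would deliver.** Approximate 95% CI for an assumed observed ICC of 0.5 by Fisher's transformation, tanh(atanh 0.5 ± 1.96/√(n − 3)):
- n = 40: tanh(0.549 ± 0.322) = 0.22 to 0.70.
- n = 20: tanh(0.549 ± 0.475) = 0.07 to 0.77.

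These intervals are wide, but they answer the question asked.

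**First sensation.** Both Outcome 2B parameters require the participant to report a sensation. The protocol gives neither the split between AIS A and B nor the share who feel bladder filling, so no loss can be calculated.

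**The case against.** The strongest reply is that the visit numbers look like leftovers from an older schedule. The sessions are labelled UDS 1 and UDS 2, so the intended data can be identified. That stands: a reader might infer that the analysis would have no data, but the protocol schedules both sessions and the error is one of reference. It still has to be corrected, since an analyst following the Statistical Plan would look in the wrong place.

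Several stronger readings are tempting, and the protocol does not support them:

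- *That the plan declares non-significance to be reproducibility.* It states no decision rule. The supportable point is that the only method named for the between-session comparison carries no information on agreement.
- *That Hypothesis 2B could never be refuted.* The hypothesis also covers improvement and the absence of adverse cardiovascular events. If the within-session comparison is stimulation off against on, a lack of improvement in one or both sessions would count against it, as would such an event.
- *That a non-significant result is 99% certain because Kruskal–Wallis is used.* The protocol attaches that test to the sentence on Aims 2A and 2C and does not repeat it for repeatability. Its simulated null rejection rates of 0.010 and 0.001 belong to paired readings correlated at 0.5 and 0.7 with n = 26, not to the case of no agreement.
- *That 10, 20 or 30 of the 40 would be evaluable.* Such counts need an assumed AIS A share and treat AIS grade as a measure of bladder sensation, which the protocol does not do. The Urodynamics section in fact expects some participants to report fullness.

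An agreement statistic might also appear in an analysis plan that is not shown. That does not remove the wrong aim and visits, or the unsuitable test, that the protocol itself states.

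**Conclusion.** The concern holds in two parts. The aim and visit references contradict the rest of the protocol; this is certain from the text and needs no assumption. The between-session method cannot measure reproducibility of individual changes: with equal session means its result is non-significant about 95% of the time at every ICC from 0 to 0.9. That figure rests on a valid 5% test and no session shift; the 0.3 SD shift and the ICC values are illustrations. The within-session comparison remains useful for showing improvement at each session.

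The dependence on first sensation is a secondary point whose size is unknown. The consequence is confined to Aim 2B of a pilot and proof-of-concept study; the sample size of 26 was not derived from it.

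**What to change.** In the Statistical Plan:

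1. Relabel repeatability as Aim 2B and refer to UDS 1 and UDS 2 in place of visit numbers, so that the text is right for both pathways.
2. For each person, compute the stimulation-on minus stimulation-off change at each session.
3. Report the mean difference between the two sessions' changes with a 95% CI, and one agreement measure: the ICC with 95% CI, or the within-person SD with limits of agreement.
4. Keep a paired within-session test of improvement for the question of whether the effect appears each time.
5. Report how many participants have both first-sensation parameters at both sessions. Where comparable on and off values exist at both sessions, also analyse the other Outcome 2A parameters.

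Items 1 to 4 cost text and a little analysis on data already planned. Item 5 is not assured to be free: according to the Urodynamics section, the stimulated run starts from a bladder prefilled to 50–75% of capacity, so a stimulated maximum volume comparable with the unstimulated one may not exist. The other downside is precision, since intervals will probably be wide at 40 participants or fewer.

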### Urodynamics

Participants will undergo standard clinical procedures for UDS, including cystometry with water at 21°C and a filling rate of < 30 mL per minute through a 6F double lumen catheter with the participants in the supine position. Abdominal pressure will be measured with a 10F intrarectal balloon catheter. Pelvic floor electromyography will be recorded during cystometry with a surface electrode placed on the

perineum. Filling will be stopped when the participants report a sensation of fullness, at the moment of urine leakage, if blood pressure reaches levels of 180/110 mmHg, or per the request of the patient.

Following the standard clinical assessment UDS we will perform UDS with TCSCS. To assess the efficacy of short-term TCSCS' on LUT function, we will first prefill the bladder (i.e. 50-75% of cystometric capacity from the first UDS) without eliciting detrusor overactivity or autonomic dysreflexia. Then, TCSCS (as described above) will be delivered for 60 s each interspersed with 30 s rest (i.e. no stim) to optimize the configuration for each individual. Stimulation frequency and location will be guided by the results of the Baseline EMG Mapping of Spinal Cord Segments performed during visit 3.

TCSCS will be stopped when the participants report a sensation of fullness, at the moment of urine leakage, if blood pressure reaches levels of 180/110 mmHg, or per the request of the patient.

Urodynamics will be performed by a trained clinician (MD or RN) under the supervision of [name] (MD), who is a urologist.

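### The Statistical Plan promises a same-session repeatability analysis, but the urodynamic session as described has no replicate stimulated measurement, so that analysis would test the stimulation effect and not repeatability

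*Protocol*

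**What the plan says.** **Statistical Plan.** The repeatability data, labelled there as Aim 2A, "will be assessed within (same session) and between (different sessions) visits (2 and 3") by a repeated-measures rank ANOVA. The sentence before it has already given the comparisons with and without stimulation, and between stimulation configurations, to Aim 2A.

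**Objectives, Hypotheses and Outcomes.** Repeatability is Objective 2B: "To test whether targeted short-term TCSCS will repeatedly improve UDS parameters across different stimulation sessions". Outcome 2B reads: "Reproducibility of changes within urodynamic parameters during stimulation will be assessed during two consecutive urodynamic procedures". Its parameters are the volume and the intravesical pressure at first sensation.

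**Urodynamics (Procedures).** The session has two parts: "Following the standard clinical assessment UDS we will perform UDS with TCSCS". For the second part, "we will first prefill the bladder (i.e. 50-75% of cystometric capacity from the first UDS"), and stimulation then "will be delivered for 60 s each interspersed with 30 s rest (i.e. no stim) to optimize the configuration for each individual".

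**Visits 4, 5, 6.** Every participant has two urodynamic sessions, UDS 1 and UDS 2. They fall at Visits 4 and 5 in Pathway 1 and at Visits 5 and 6 in Pathway 2.

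**The concern.** A within-session repeatability analysis needs the same quantity measured at least twice under the same conditions in one session. The quantity here is the change under stimulation, and the session described supplies it once. A repeated-measures test on the same-session data then has only efficacy contrasts to work on.

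Two things are at stake. A result labelled repeatability could be reported that is really a second run of the Aim 2A test. And the within-session error, against which between-session variation might be judged, cannot be estimated from what is described. A later analysis plan cannot repair this, because it cannot create replicates that the session did not collect.

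**Working it through.** **1. The protocol's own figure.** The Statistical Plan gives a minimum of 26 participants for a change in voiding efficiency from 37.8 ± 40.6% (off) to 58.2 ± 39.4% (on).

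- Difference: 58.2 − 37.8 = 20.4 points.
- Effect size: 20.4 / √[(40.6² + 39.4²)/2] = 20.4 / 40.0 = 0.51, as stated.
- A one-sided paired t-test at α = 0.05 with this effect size reaches 80% power at n = 26 (power 0.81). A two-sided test needs 33. Sidedness is not stated.

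So 26 is reproduced, and it sizes an off-versus-on effect. No figure in the protocol sizes repeatability.

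**2. What one session yields, as described.**

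| Part of the session | Stimulation | Values of each Outcome 2B parameter |
|---|---|---|
| Standard study | off | 1 |
| Study with stimulation | on, 60 s bouts used to find a configuration | at most 1 |

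First sensation occurs once per fill. The on count is at most one because the stimulated part starts from a bladder already filled to 50–75% of capacity, and the protocol does not say how first sensation is timed against that prefill.

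- Change scores per participant: 1 per session × 2 sessions = 2.
- Same-session replicates of a change score described: 1 − 1 = 0.

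**3. What the same-session test can compare.** Two contrasts remain: off against on, and configuration against configuration. Both are Aim 2A comparisons under the preceding sentence of the Statistical Plan.

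**4. What each contrast responds to.** A simulation of 2,000 trials per setting used SD 40, correlation 0.5 between all four measurements (off and on in each of two sessions), a mean effect of 20.4 points identical in both sessions, and two-sided 0.05. Pairs were compared with the Wilcoxon signed-rank test and all four cells with the Friedman test.

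| Comparison | Rejects, n = 26 | Rejects, n = 40 |
|---|---|---|
| Off against on, same session | 68% | 88% |
| All four off/on measurements | 76% | 93% |
| On in UDS 1 against on in UDS 2 | 5% | 5% |
| Change in UDS 1 against change in UDS 2 | 5% | 5% |

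With no effect, every row is at 5 to 6%. The first two rows follow the stimulation effect. They are power figures for an efficacy test, not error rates for repeatability.

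**5. Why a difference test between sessions is not enough either.** In the same simulation, the covariance between a participant's two change scores is

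cov(on₁ − off₁, on₂ − off₂) = 40² × (0.5 − 0.5 − 0.5 + 0.5) = 0.

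The variance of each change is 2 × 40² × (1 − 0.5) = 1,600, so its SD is 40. The ICC of the individual change is therefore 0 / 1,600 = 0: a participant's response in UDS 1 says nothing about that participant's response in UDS 2. The between-session test still rejects only 5% of the time, because the mean change is the same. Repeating the check at n = 40 with an ICC of 0.9 gave about 6%. The test cannot tell an ICC of 0 from one of 0.9.

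**6. Precision of the agreement measure.** With one difference of change scores per participant and the mean session shift removed, the degrees of freedom are n − 1. The 95% limits of the within-subject SD are the estimate times √(df/χ²).

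- n = 40: √(39/58.12) = 0.82 to √(39/23.65) = 1.28.
- n = 26: √(25/40.65) = 0.78 to √(25/13.12) = 1.38.

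**7. References in the same sentence.** Visit 2 is the baseline questionnaire and blood-pressure visit, and Visit 3 is the EMG mapping visit. The Visits 4, 5, 6 section places urodynamics at Visits 4 and 5 or 5 and 6. Repeatability is Objective 2B, not 2A.

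**The case against.** **The protocol does not exclude repeats.** This is right. Several bouts are given in the stimulated run, and nothing forbids giving a configuration twice. A reader might infer that no configuration is repeated, but that would be an inference from silence. What stands is narrower: no replicate is planned or described, and the bouts have another stated purpose ("interspersed with 30 s rest (i.e. no stim) to optimize the configuration for each individual").

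**No rule says that a significant within-session result counts against repeatability.** Also right. A reader might infer that an effective stimulation would be read as poorly repeatable, and might take the rejection rates above as the size of that harm. The documents do not support this. They give no decision rule, and Objective 2B equally permits the reading that an off-to-on improvement seen in each session is a repeated improvement. The rates also depend on the test assumed and on an effect size that belongs to voiding efficiency, not to either Outcome 2B parameter.

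**Aim 2B can still be assessed.** It can. Both sessions are planned for every participant, so the defect is limited to the same-session half and to the choice of a difference test.

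**This is analysis-plan detail in a pilot.** Partly. Which agreement statistic to use is commonly settled later. But the protocol itself has fixed a same-session repeatability analysis and a rank test for it, and its session does not supply the data.

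**Conclusion.** The point holds in limited form. The protocol commits to a same-session repeatability analysis for which its session, as described, supplies zero replicate change scores per participant. That analysis would repeat the Aim 2A contrasts. The between-session data suit Objective 2B, but a rank test of differences does not measure agreement, as step 5 of the check shows.

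This rests on reading the Urodynamics section as a full account of the session and on Outcome 2B's two procedures being UDS 1 and UDS 2. The second reading is the natural one, since both procedures must include stimulation. If the sponsor does plan a same-session repeat, the missing item is its description.

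The wrong aim label and the mismatched visit numbers follow directly from the text. The visit numbers may come from a different numbering scheme, which the document cannot settle. The matter is worth correcting because it affects a stated objective at little cost. It does not undermine Aim 2A or the sample size.

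**What to change.** In the Statistical Plan:

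1. Delete the same-session part of the repeatability analysis. Keep off-versus-on and configuration contrasts under Aim 2A.
2. Analyse Aim 2B as agreement of the off-to-on change between UDS 1 and UDS 2, reporting the within-subject SD or an ICC with its confidence interval for each of the two Outcome 2B parameters. Name the stimulated value that enters the change in each session.
3. Change the aim label from 2A to 2B.
4. Reconcile the visit numbers with the Visits 4, 5, 6 section (Visits 4 and 5, or 5 and 6).

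This changes wording and analysis only, with no added visit or measurement. The price is the within-session repeatability claim. If the sponsor wants to keep that claim, the Urodynamics section would have to describe the same-session replicate before data are collected. With 40 participants the within-subject SD is known to about −18% to +28%, and with 26 to about −22% to +38%, which is adequate for a pilot that estimates agreement.
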